## Abstract

**Background:**

Delirium is a frequent complication in comatose Out‐of‐Hospital Cardiac Arrest (OHCA) survivors requiring postresuscitation intensive care and is associated with higher mortality and longer hospitalization. Despite this, there is no established pharmacologic strategy for delirium prevention in OHCA survivors. This trial aims to evaluate if prophylactic use of olanzapine in comatose OHCA patients can reduce delirium incidence, thereby leading to a shorter duration of hospitalization.

**Methods:**

The Danish Out‐of‐Hospital Cardiac Arrest (DANOCHA) trial is an investigator‐initiated, multicenter, randomized, controlled trial evaluating four postresuscitation interventions in adult patients resuscitated after OHCA including administration of prophylactic olanzapine compared with placebo. Comatose adult patients with OHCA of presumed cardiac cause and sustained return of spontaneous circulation (> 20 min) will be randomized 1:1 to receive either 10 mg of olanzapine or placebo immediately after inclusion in the trial and the two following evenings for a total of three doses. The primary outcome is days alive and out of the hospital within 30 days after admission. Analysis of primary outcome will be analyzed using the Wilcoxon rank‐sum test. Results will be presented as medians with interquartile ranges and 95% confidence intervals for the median difference. Inclusion began in June 2023, and the study aims to include 1000 patients from five sites over an estimated time period of 3–4 years. The trial is registered at clinicaltrials.gov (identifier: NCT05895838) and euclinicaltrials.eu (2024‐515997‐28‐00).

**Perspectives:**

Optimizing postresuscitation care through large‐scale randomized trials is essential for improving outcomes of OHCA survivors. The findings from this part of the DANOHCA trial will provide evidence regarding the effects of prophylactic olanzapine in comatose OHCA survivors.

**Trial Registration:** EudraCT no 2016‐003265‐26; EU CTIS no 2024‐515997‐28‐00; ClinicalTrials.gov identifier NCT05895838

## Introduction

1

In Europe, the incidence of Out‐of‐Hospital Cardiac Arrest (OHCA) is approximately 55 per 100.000 inhabitants, and in Denmark more than 5.000 individuals suffer from OHCA yearly, with most cases having a presumed cardiac etiology. Improved prehospital logistics and bystander‐performed basic life support have considerably improved the outcome over the last decades. However, the 30‐day mortality rate remains above 80% [1]. For unconscious patients with OHCA who are resuscitated successfully and admitted to an intensive care unit (ICU), the 30‐day mortality remains at approximately 50% with the main cause of death being irreversible brain injury [2].

Intensive care following resuscitation from OHCA is based on a set of interventions aimed at circulatory stabilization and mitigation of anoxic brain injury [3, 4]. Patients frequently experience postcardiac arrest syndrome and persistence of the condition that precipitated the cardiac arrest [5]. These patients are often admitted to hospital in an unstable condition necessitating both circulatory and respiratory support.

With the nationwide DANOHCA trial we seek to evaluate four new potential interventions for improving outcomes after OHCA. A separate protocol manuscript will be published for each intervention, with the present manuscript describing the intervention of prophylactic olanzapine compared to placebo for reducing delirium incidence and shortening hospitalization (LINK; Dexamethasone, Wake‐up call, Backrest).

### Preventing Delirium With an Antipsychotic Drug

1.1

Delirium is an acute, fluctuating, and reversible syndrome characterized by impaired cognition and/or consciousness accompanied by troubles maintaining attention and potential visual and auditory hallucinations [6]. It is the most common sign of acute brain dysfunction among critically ill patients [7]. After awakening, hyper‐ and hypoactive delirium is commonly encountered in all critically ill patients treated with mechanical ventilation in an ICU [8]. Delirium is associated with higher mortality, longer ICU and hospital stays, risk of unplanned removal of devices, and poorer compliance with physical therapy [9, 10]. This is even more pronounced in patients resuscitated after cardiac arrest, where the hypoxic brain injury per se induces brain dysfunction [11]. The optimal management of delirium is uncertain. A study comparing treatment with haloperidol, ziprasidone, or placebo failed to prove benefit of the antipsychotic treatment compared with placebo in critically ill patients with manifest delirium [12]. A more recent trial assessing only haloperidol also failed to prove that haloperidol led to a significantly shorter duration of hospitalization compared to placebo [13].

Limited data exists on prophylactic use of antipsychotics to prevent delirium in critically ill patients, and no studies have tested prophylactic use in OHCA survivors specifically. Prophylactic administration of antipsychotics may be indicated in high‐risk postoperative patients, but there is no evidence currently supporting this approach for OHCA survivors [14, 15]. Olanzapine is an atypical antipsychotic agent of the thienobenzodiazepine class that blocks multiple receptors including dopaminergic, serotonergic, adrenergic, histaminic, and muscarinic. Olanzapine has been suggested to alleviate delirium as well as nausea, vomiting, and pain [16]. Early prophylactic treatment with olanzapine could therefore reduce the number of patients developing delirium, thereby improving the rehabilitation leading to shorter duration of hospitalization.

This part of the DANOHCA trial aims to fill this research gap by evaluating the efficacy of prophylactic use of olanzapine in adults who remain comatose after resuscitation from OHCA. We hypothesize that prophylactic use of olanzapine reduces the number of patients developing delirium, thereby leading to a greater number of days alive and out of the hospital within 30 days in an intention‐to‐treat (ITT) analysis.

## Methods

2

### Trial Design

2.1

This study is an investigator‐initiated, randomized, controlled, multicenter clinical trial with co‐enrolment into four different interventions: (1) olanzapine or placebo, (2) dexamethasone or placebo, (3) backrest elevation to 35° or 5°, and (4) early (≤ 6 h) or late (28–36 h) wake‐up call. Intervention‐specific rationale and procedures are described in four corresponding protocol manuscripts (LINK; Dexamethasone, Wake‐up call, Backrest) and a statistical analysis plan (SAP) that outlines the methodological approach to analyzing the common primary, secondary, and tertiary outcomes of the DANOHCA trial (LINK; SAP). Patients and members of the public were not involved in the design of the trial due to the emergency nature of OHCA and the inability of patients to participate in the planning process.

After completion of screening procedures, patients are randomized in a 1:1 fashion to receive either the active intervention or placebo/control intervention for each of the four interventions. The randomization sequence was developed using the PROC PLAN procedure in SAS (SAS Institute Inc., Cary, NC, USA). The randomization is revealed by opening a sealed box containing allocation to backrest positioning, time for wake‐up call, and blinded vials/tablets for dexamethasone and olanzapine respectively, as well as a unique trial identifier and a QR code for data entry into the electronic case report form (eCRF). The study is not stratified by trial site as sealed boxes are prepared centrally and delivered to trial sites randomly upon the inclusion rate.

The DANOHCA trial is registered at clinicaltrials.gov (identifier: NCT05895838) and at the EU CTIS under 2024‐515997‐28‐00, accessible at euclincaltrials.eu (previously registered with EudraCT number: 2021‐005876‐21 at clinicaltrialsregister.eu). The trial has been approved by the Danish Medicines Agency (DKMA) and Danish Medical Research Ethics Committees in accordance with the Clinical Trials Regulation No. 536/2014 and registered with CTIS Trial number 2024‐515997‐28‐00; Transition authorized with conditions on 11‐10‐2024; the current protocol v02‐12‐2025 (SM‐2) was authorized on 05‐12‐2025. Prior to the transition to CTR the trial had been approved by the Danish Medicines Agency no. 2021121966 since 07‐02‐2022 and the regional ethics committee of the Capital Region journal number H‐21077461 since 08‐07‐2022. The full study protocol is available on the study website under the “Trial Documents” section [17].

### Trial Conduct

2.2

The trial is conducted according to all applicable national and international legislation and guidelines including the revised Declaration of Helsinki [18] and the international Good Clinical Practice guidelines [19]. The trial and protocol were developed in accordance with the International Conference on Harmonization (ICH) guidelines [19, 20, 21] and the Standard Protocol Items: Recommendations for Interventional Trials (SPIRIT) statement [22, 23]. A completed SPIRIT 2025 checklist is provided in Supporting Information. The trial adheres to EU and national legislation on medical research in patients in emergency situations who are temporarily incapacitated and unable to provide informed consent [24, 25, 26, 27]. The trial is approved as emergency research with proxy consent, as the interventions should be started without delay. Informed consent is obtained from an appointed legal representative, and subsequently from the next of kin as soon as possible. Informed consent is obtained from the patient at the earliest opportunity after the patient regains capacity. All consenting parties may withdraw their consent for trial participation at any time. Screening is performed as soon as possible after hospital admission by the physician in charge. The screening log includes all patients admitted to ICU after OHCA with inclusion of the patient's ID, demographic data, and reasons for the exclusion of screened patients (lack of inclusion criteria, presence of exclusion criteria, or logistical reasons).

During ICU‐stay, included patients are screened for delirium three times daily by clinical staff using the delirium screening tool Confusion Assessment Method for the Intensive Care Unit (CAM‐ICU) [28]. Delirium is considered to be present if a patient has a positive CAM‐ICU assessment.

### Trial Intervention

2.3

Upon ICU admission, patients are randomized in a 1:1 ratio to receive either the active intervention or a matching placebo/control intervention for each of the four trial interventions. Thus, the trial is designed as a 2 × 2 × 2 × 2 factorial randomized trial, with the four interventions reported as separate trials. The balance of allocation across the 16 possible treatment combinations is monitored during generation of the randomization sequence and as part of the planned interim analyses.

For this intervention within the DANOHCA trial, patients will receive either a dose of 10 mg olanzapine (Olanzapin, Stada Arzneimittel AG, Germany) or matching placebo administered by feeding tube upon ICU admission. The patients will receive 10 mg olanzapine or matching placebo the following two evenings at 6.00 p.m. for a total of three doses. If patients wake up and are extubated, the study drug is continued for three administrations unless patients are discharged from the ICU before the final administration. Prior to randomization, patients will be excluded if Long QT Syndrome has been confirmed or suspected because of potential QT‐prolonging effect and concerns for arrhythmia. All patients are monitored by mandatory telemetry of heart rhythm for 96 h or until life sustaining therapies are withdrawn. In the event of delirium, patients are treated according to local practice at the enrolling site, most often including dexmedetomidine, haloperidol, or midazolam.

### Blinding

2.4

The olanzapine versus placebo intervention is blinded to both clinical personnel, site investigators, and statisticians. The study drug of olanzapine will be delivered by The Hospital Pharmacy of the Capital Region. Packaging into sealed boxes is performed by trained healthcare professionals and will be validated by another staff member before the box is sealed. The study boxes with the olanzapine intervention contain an opaque container with three tablets of either olanzapine or placebo. Preparation of study drugs for administration will be performed by a nurse at the admitting site who is not involved in the clinical care of the patient. The drug administration schedule will be identical for both active medication and placebo and registered both in medical records and study eCRF for monitoring of adherence. During the conduct of the trial, treatment allocation will remain concealed and will only be unblinded in the event of a serious adverse event (SAE) or a suspected unexpected serious adverse reaction (SUSAR) at the discretion of the trial sponsor.

### Patient Eligibility and Enrollment

2.5

The trial is coordinated and led by The Department of Cardiac Intensive Care, Copenhagen University Hospital—Rigshospitalet, Copenhagen, Denmark. Comatose patients resuscitated after OHCA with a suspected cardiac etiology are enrolled consecutively at five university hospitals representing the five Danish health regions: Copenhagen University Hospital—Rigshospitalet, Aalborg University Hospital, Aarhus University Hospital, Odense University Hospital, and Zealand University Hospital—Koege.

All patients with OHCA admitted to one of the five participating ICUs are screened for inclusion. Eligible OHCA patients fulfilling all inclusion criteria and no exclusion criteria (Table 1 Inclusion and exclusion criteria) are included as soon as possible and no later than 3 h after ROSC. Immediately after inclusion in the trial, a sealed box containing trial medication and allocation group for the two physical interventions is opened, and the four interventions are initiated. Co‐enrollment in other trials must be permitted by the steering group following careful evaluation of the risk of interaction with the four per‐protocol interventions.

**TABLE 1 aas70289-tbl-0001:** Inclusion and exclusion criteria.

Inclusion criteria	Exclusion criteria
All the listed criteria (1–4) must be met: Age ≥ 18 years OHCA of presumed cardiac cause Sustained ROSC^a^ Unconsciousness (GCS < 9) (patients not able to obey verbal commands) after sustained ROSC at the time of randomization	Females of childbearing potential if pregnancy is suspected (unless a negative HCG test can rule out pregnancy within the inclusion window) Known bleeding diathesis (medically induced coagulopathy (e.g., warfarin, NOAC, clopidogrel) does not exclude the patient) Suspected or confirmed acute intracranial bleeding Suspected or confirmed acute stroke Unwitnessed asystole Known limitations in therapy and Do Not Resuscitate‐order Known disease making 180 days survival unlikely Known prearrest cerebral performance category (CPC) 3 or 4 functional status > 3 h (180 min) from ROSC to screening Systolic blood pressure < 80 mmHg despite fluid loading/vasopressor and/or inotropic medication^b^ Use of intra‐aortic balloon pump/axial flow device/ECMO^c^ Temperature on admission < 30°C. Known allergy for dexamethasone or olanzapine Ongoing (within 48 h) treatment with olanzapine or dexamethasone Known back or hip condition that precluded the patients from being positioned with backrest from 0° to 45° angle Known or suspected Long QT Syndrome (LQTS) Known active fungal disease. Localized skin lesions do not exclude patients from inclusion Estimated body weight < 45 kg

*Note:* Since postresuscitation care and intervention are regarded as emergency procedures and should not be delayed, there should only be taken easily accessible sources (previous in‐house chart records, history from emergency medical services) to assess Criteria 2, 5, 6, 7, 8, 12, 13, 14, and 15.

^a^
Sustained ROSC: sustained ROSC is when chest compressions or mechanical circulatory support have been not required for 20 consecutive minutes and signs of circulation persist.

^b^
If the systolic blood pressure (SBP) is recovering during the inclusion window (180 min) the patient may be included.

^c^
If the patient is weaned and the device is removed during the inclusion window (180 min), the patient may be included.

### Outcomes

2.6

#### Primary Outcome

2.6.1

The primary outcome for the study is days alive and out of the hospital within 30 days in the two treatment arms, as a modified intention to treat (ITT) analysis. The primary outcome is determined as follows: A day (≥ 24 h) spent at health care facility is counted as time in hospital. Outpatient visits and brief hospitalizations for less than 24 h are not counted as days in hospital. Days admitted to hospital or as deceased within 30 days from randomization are subtracted from 30 days and the result is rounded down to the nearest whole number of days. For patients dying during initial 30 days, the time spent alive outside of hospital is retained for the outcome calculation.

#### Secondary Outcomes

2.6.2

Secondary outcomes are:
All‐cause mortality at 90 days.Number of CAM–ICU negative days at 30 days.Number of days without pharmacological treatment for delirium (other than study drug during the intervention period).Number of patients with one or more serious adverse reactions to olanzapine in the ICU.Cerebral performance category (CPC) and modified Rankin scale (mRS) at follow‐up 3–6 months after cardiac arrest (conducted either through physical attendance or telephone interview according to participant preference).

#### Exploratory Outcomes

2.6.3

Exploratory outcomes are as follows:
Serum neuron‐specific enolase [29] (NSE) at 48 and 72 h [30].Number of CAM‐ICU positive patients 48 h after randomization.ICU length of stay.Hospital length of stay (including in‐patient rehabilitation and transfer to referral hospital).Number of patients receiving rescue medication.Number of days with rescue medication per patient.

### Statistical Methods

2.7

#### General Principles

2.7.1

The four interventions in the DANOHCA trial are considered as four individual trials, and data will be analyzed and reported individually; hence, no adjustment for multiple comparisons is planned for the primary outcome. A full statistical analysis plan is published together with the four separate protocol articles (LINK: SAP). Since previous trials in patients after OHCA predominantly yielded neutral results, all four interventions are accepted without consideration of potential interactions. If more than one intervention demonstrates a nonneutral effect, a post hoc evaluation of possible interactions and potential safety aspects will be conducted and reported. Also, as an investigation of potential safety issues related to possible interactions between the four interventions, we will report interactions in relation to mortality and the occurrence of other SAE. All regression analyses will be adjusted for site as a covariate.

All analyses will be conducted according to the modified ITT principle, including all randomized participants who meet the inclusion criteria and have available outcome data, or imputed outcome data (see Section 2.7.5). Throughout, categorical variables will be presented as counts with proportions, whereas continuous variables will be presented as mean ± SD if normally distributed, and as median (25–75th percentile) if nonnormally distributed, as evaluated by quantile–quantile plots. The primary analysis of the primary outcome will include the modified ITT population. Further, we plan a sensitivity analysis in the per protocol population to assess the effect. The per protocol cohort will be defined as only those trial participants who have received all scheduled doses of the pharmacologic intervention with olanzapine.

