#### Monitoring of AE and SAE

2.11.2

Patients are monitored for the development of an AE for 30 days after randomization or until hospital discharge if this occurs later than 30 days. A prespecified form in the eCRF allows for daily recording of AE during ICU‐stay. AE occurring after discharge from the ICU and within 30 days from randomization will be evaluated at the time of ambulatory follow‐up (scheduled for 3–6 months after cardiac arrest). AE will only be reported to the trial sponsor if they can be classified as a SAE with a suspected direct relation to the trial intervention. Once a year all SAEs occurring at the trial centers will be submitted and a safety report of all trial patients will be submitted to the competent authorities as required. All SAEs will be reported as outcome measures in the final trial report. Monitoring of the trial is performed by the Danish Good Clinical Practice (GCP) units according to preplanned monitoring plans at the participating sites.

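### The rule placing all analyses on the modified ITT set also covers the safety outcomes, so dosed patients later judged to fail an inclusion criterion would leave the safety comparison

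*Protocol article*

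**What the plan says.** General Principles (2.7.1) fixes one analysis set for the whole trial: "All analyses will be conducted according to the modified ITT principle, including all randomized participants who meet the inclusion criteria". Members must also "have available outcome data, or imputed outcome data". The section then repeats the set for efficacy: "The primary analysis of the primary outcome will include the modified ITT population". The only other set defined is narrower and serves a sensitivity analysis: "The per protocol cohort will be defined as only those trial participants who have received all scheduled doses".

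Three statements on safety bear on this rule:

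- Secondary Outcomes (2.6.2) lists "Number of patients with one or more serious adverse reactions to olanzapine in the ICU".
- General Principles (2.7.1) announces, as a safety investigation across the four interventions, that "we will report interactions in relation to mortality and the occurrence of other SAE".
- Monitoring of AE and SAE (2.11.2) promises: "All SAEs will be reported as outcome measures in the final trial report". It names no analysis set or denominator.

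On timing, Patient Eligibility and Enrollment (2.5) says: "Immediately after inclusion in the trial, a sealed box containing trial medication and allocation group for the two physical interventions is opened". All four interventions then start.

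**The concern.** For a drug-safety outcome, the patients who matter are those exposed to study drug, whether or not they later prove to have been eligible. The rule in 2.7.1 selects on eligibility instead. Because the box is opened straight after inclusion, a failed inclusion criterion that comes to light later will usually do so after the first dose. Such a patient is exposed but lies outside the only set on which safety is to be compared.

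At stake is the completeness of the one listed secondary outcome specific to olanzapine harm. When events are few, losing even one from numerator and denominator can change how the comparison reads, and the exclusion brings no gain in return. Restoring full ITT for the primary outcome would not by itself settle this, because the safety set should follow exposure.

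**Working it through.** **1. Does the rule reach safety?** Its subject is every analysis. The serious-adverse-reaction count is a listed secondary outcome, and the SAE interaction reporting is announced in the same section as the rule. No sentence in the Methods exempts either, and no as-treated or safety set is defined. The per protocol cohort cannot fill the gap because it requires all scheduled doses.

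**2. Who is removed?** The rule names only the inclusion criteria. Table 1 has four: age, presumed cardiac cause, sustained ROSC, and unconsciousness at randomisation. Exclusion criteria form a separate list, and Trial Conduct (2.2) treats missing inclusion criteria and present exclusion criteria as distinct reasons for not enrolling. A dosed patient later found to breach an exclusion criterion therefore stays in the set on the literal wording.

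**3. Set against 2.11.2.** An SAE in a dosed patient who failed an inclusion criterion is promised as an outcome measure there, yet 2.7.1 keeps that patient out of every analysis. The two can coexist only if such events are listed outside the arm comparison, and the article does not say so.

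**4. Size.** The document gives neither the share of randomised patients who fail an inclusion criterion nor the serious-reaction risk. Both ranges below are assumptions, for illustration only.

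- Planned enrolment (2.12): 1000, allocated 1:1 (2.1), so about 500 on olanzapine.
- Assumed share failing an inclusion criterion, 1-5%: 1000 × 0.01 = 10 to 1000 × 0.05 = 50 patients, of whom about 5 to 25 are on olanzapine.
- Assumed serious-reaction risk on olanzapine, 1-5%: expected loss 5 × 0.01 = 0.05 to 25 × 0.05 = 1.25 patients with a reaction.
- Chance of losing at least one, 1 − (1 − r)^m: 1 − 0.99^5 = 0.049 to 1 − 0.95^25 = 0.723.

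**5. Effect on the primary outcome.** The plan's own sample size reproduces. A difference of 1.5 days, SD 7, two-sided 5% and 90% power give 458 per arm, 916 in total, against the stated 920; power at 920 is 90.1%. At 1000 patients power is 92.3%, and removing 1-5% of them leaves 92.1% to 91.0%. The issue is completeness of safety data, not power.

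**The case against.** The strongest reply is that few patients can be affected. The inclusion criteria are largely judged at entry: cardiac cause need only be presumed, and unconsciousness is assessed at randomisation, so a later non-cardiac diagnosis need not count as a failure. This stands, and it is why the point is minor.

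A reader might infer that the rule discards the patients in whom olanzapine harm is of most interest, such as those with Long QT Syndrome, olanzapine allergy or low body weight. The document does not support that. These are exclusion criteria, and the rule as worded leaves such patients in.

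A reader might also take the note to Table 1, which limits some checks to easily accessible sources, as evidence that many dosed patients will fail. That does not follow either. At least eight of the nine criteria it numbers must be exclusion criteria, since only four inclusion criteria exist, and the remaining one (number 2) is naturally read the same way.

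It can also be said that safety populations belong in the SAP, which is not shown and may define one. That would answer a complaint that a safety set is missing, which is not the complaint here. The article states a universal rule. If the SAP has an exposure-based set, this sentence contradicts it; if not, the rule applies as written.

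Finally, 2.11.2 requires all SAEs in the final report and an annual safety report on all trial patients. That limits the harm, since the events need not go unreported, but it does not say on which patients the arms are compared.

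**Conclusion.** The point holds as a minor defect of wording. As written, the modified ITT rule governs the serious-adverse-reaction outcome and the SAE analyses. It would drop from them any patient who received study drug and was later judged not to have met one of the four inclusion criteria, in tension with 2.11.2.

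The number affected cannot be computed from the document and is probably small. The range of 0.05 to 1.25 olanzapine patients with a reaction rests wholly on the assumed 1-5% rates, for which the article offers no support. The document does not show that SAEs will be concealed or left unreported, or that patients breaching exclusion criteria will be removed.

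**What to change.** In 2.7.1:

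- Limit the modified ITT rule to efficacy outcomes.
- State that serious adverse reactions and SAEs in the olanzapine comparison are analysed in all randomised patients who received at least one dose of study drug (olanzapine or placebo), regardless of later eligibility findings and where consent permits use of the data.
- State that the SAE and mortality interactions across the four interventions are analysed in all randomised patients as allocated. Two of the four interventions are not drugs, so these analyses should not depend on olanzapine dosing.
- Reconcile 2.7.1 with 2.11.2 by naming the set on which SAEs are compared, and carry the same wording into the SAP.

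The cost is a short addition to the text and one extra analysis flag. The downside is slightly different denominators in the efficacy and safety tables, which a footnote can explain. No sample-size figure changes.
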